## Methods/Design

### Design

This trial is an open-label multicenter randomized controlled trial with four parallel arms. We compare the affected meridians with non-affected meridians, sham acupuncture and waiting-list groups as well. The trial is performed in the following Hospitals: First Affiliated Hospital of Chengdu University of Traditional Chinese Medicine; Third Affiliated Hospital of Chengdu University of Traditional Chinese Medicine (TCM); Affiliated Hospital of Ningxia Medicine University; First Affiliated Hospital of Hunan University of TCM; Second Affiliated Hospital of Hunan University of TCM; Affiliated Hospital of Hunan University of TCM - Hengyang Hospital; Chenzhou No.1 People’s Hospital; First Affiliated Hospital of Guiyang College of TCM; Second Affiliated Hospital of Guiyang College of TCM; Yunnan Provincial Hospital of TCM; and Second Affiliated Hospital of Shanxi College of TCM.

The whole study period is 13 weeks,with a 1-week run-in period, 6-week treatment phase, and 6-week follow-up phase. After randomization, patients in acupuncture groups will receive 18 sessions of treatment over a 6-week treatment period. Participants in the waiting-list control group will give an option to receive acupuncture treatment after 13 weeks study period. Outcome measurements will be assessed at day 0, 6 weeks, 9 weeks, and 12 weeks after randomization. All patients will be informed that they may be randomly allocated to affected meridian acupuncture group, non-affected acupuncture group, invasive sham acupuncture group, or waiting-list group (Figure 1, Table 1). This trial will be conducted according to the principles of the Declaration of Helsinki (version Edinburgh 2000). The trial protocol has been approved by the regional ethical review committee of traditional Chinese medicine in Sichuan Province on April 2012. We will require all patients to sign the written informed consent, and they will be given enough time to decide whether they will take part in this trial. This trial started in September 2012, and will be completed in December 2017.

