**Primary endpoint** The primary outcome measurement in this study is the change in average 24-hSBP and DBP before randomization and 6 weeks after randomization. Ambulatory mean blood pressure (ABPM) is superior to clinic BP in the prediction of cardiovascular morbidity and mortality [18,19]. Because ABPM exerts a different predictive effect on the cardiac and cerebrovascular complications [20] we selected ABPM as our primary endpoint.

##### 

**Secondary outcome measures** Ambulatory pulse pressure (APP) [21] is a well-established marker of cardiovascular risk. We choose APP as one of the secondary endpoints to evaluate the effect of acupuncture for hypertension. There is a prospective study [22] that shows that both high ABPM values and abnormal daytime/night-time BP profiles are associated with later occurrence of ischemic cerebrovascular and coronary events independently of casual BP values and other cardiovascular risk factors. It is therefore necessary to observe the daytime/night-time BP of hypertensive patients.

Changes in patients’ health-related quality of life, according to the SF-36 (Medical Outcomes Study 36-Item Short Form) questionnaire Chinese version is another secondary outcome measure [23]. The validity and reliability of this scale have proven in previous studies [24,25]. The scale contains eight dimensions (physical function, role physical, bodily pain, general health, vitality, social function, role emotional, mental health) and two summary components (physical and mental), measured on a scale of 0 to 100. Lower scores indicate a poorer quality of life. SF-36 investigates at 0 day and 6 weeks after randomization.

Response to the treatment will be measured at the end of treatment, using a five-point Likert self-administered scale:'Compared with pre-treatment, to what extend did you think your hypertensive symptoms change?’1, absence of all symptoms; 2, significantly improved; 3, moderately improved; 4, not changed; 5, deteriorated. 'After treatment, how do you evaluate the effect of acupuncture for hypertension?’ 1, no effect(0%); 2, a little effect(25%); 3, moderate effect(50%); 4, a significant effect (75%); 5, complete response(100%). The patients fill in this questionnaire at the end of the treatment.

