Expectation of the treatment will be measured by a self-administered questionnaire. With seven items as follows: (1) In the coming year, how will you think your disease will be relieved? (significantly(≥75%); moderately(approximately 50% to 75%); a little(approximately 25% to 50%); no change(0% to 25%)); (2) How effective do you think acupuncture is for hypertension? (significant(≥75%); moderate(approximately 50% to 75%); a little(approximately 25% to 50%); no change(approximately 0% to 25%)); (3) Which treatment options do you prefer to take as your treatment for hypertension? (acupuncture and moxibustion; herbs; Western medicine; others); (4) How familiar are you with acupuncture and moxibustion? (very familiar; so-so; a little; not at all); (5) By what means did you get to know about acupuncture and moxibustion? (friends and relatives; media reports; medical work; others); (6) How did acupuncture and moxibustion work in your memory? (excellent; good; so-so; not at all); (7) During the treatment, are you afraid of the pain or uncomfortable sensation caused by acupuncture and moxibustion? (very much; a little; never think about it; feel comfortable). The subjects will mark the best answer for each of the questions. The assessment will be performed at day 0 after randomization.

Before randomization, a special pattern identification questionnaire was developed to differentiate which syndrome the subjects pertaining to.

#### **
*Blood pressure measurement*
**

Ambulatory blood pressure measurements are performed with an oscillometric device (A&D Co.Ltd., Japan TM-2430). During a 24-h monitoring period, the device takes 76 measurements. Daytime is defined as 08:00–22:00. The measurement during the daytime will be taken every 15 min. Night-time is defined as 22:00–08:00. The measurement during the night-time will be taken every 30 min. The 24-h ambulatory blood pressure monitoring measures at baseline, 6 weeks, 9 weeks, and 12 weeks after randomization. Clinical blood pressure measurements will be taken before and after each acupuncture session with Automatic Upper Arm Blood Pressure Monitor (Omron HEM 7200, Liaoning, China).

#### **
*Participant safety*
**

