Statistical analysis protocol was designed by the Brightech-Magnsoft Data Services Company and principal investigators. Analysis of all data in this trial will be performed by the Brightech-Magnsoft Data Services Company. The data will be analyzed with SAS 9.1 and SPSS13.0 software packages. All analyses will be on the basis of the intention-to-treat (ITT) population and per-protocol (PP) population. The result of the ITT analysis will be compared with that of the PP analysis to determine whether the results are consistent. Missing data will be filled by Last Observation Carry Forward rules.

Demographic characteristics and other baseline values will be described using descriptive statistics for each group. For the primary outcome, we will run a comparison between pooled acupuncture groups and waiting list control group to figure out whether acupuncture is more effective for this condition. We will then run another comparison between the pooled acupuncture groups and sham acupuncture group to find out whether acupuncture is more efficacious. Finally, a comparison between acupuncture groups will be run to see if selecting points along meridians was a better treatment option. The above analysis will be performed using the ANCOVA model. Multiple comparisons will be adjusted according to the Bonferroni correction method.

The repeated measures analysis will be used in the different time point assessments for the secondary outcomes. The Kruskal-Wallis test will be employed in the analysis of skewed distribution data. There is a designated acupuncturist in each center to all the acupuncture treatment, which probably introduces clustering effect in this trial. Therefore, we calculated the intra-cluster correlation coefficient from the results of this trial and report the coefficient.

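### With no ambulatory reading between baseline and week 6, the last-observation rule scores every missing week-6 primary value as zero change

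*Protocol article*

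**What the plan says.** The paragraphs on sample size and statistical analysis give a single rule, with no exception for the primary endpoint: "Missing data will be filled by Last Observation Carry Forward rules".

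The primary endpoint paragraph defines the outcome as "the change in average 24-hSBP and DBP before randomization and 6 weeks after randomization". The section on blood pressure measurement gives the schedule: "The 24-h ambulatory blood pressure monitoring measures at baseline, 6 weeks, 9 weeks, and 12 weeks after randomization". The Design section agrees ("Outcome measurements will be assessed at day 0, 6 weeks, 9 weeks, and 12 weeks after randomization"), and Table 1 has no 24-h blood pressure entry at week 3.

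One other blood pressure is recorded during treatment: "Clinical blood pressure measurements will be taken before and after each acupuncture session". It comes from a different device and is tied to treatment sessions.

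For the primary comparisons the plan states: "The above analysis will be performed using the ANCOVA model". It adds: "Multiple comparisons will be adjusted according to the Bonferroni correction method". Intention-to-treat and per-protocol analyses are both planned: "The result of the ITT analysis will be compared with that of the PP analysis to determine whether the results are consistent".

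**The concern.** Last observation carried forward is usually defended on the ground that a recent on-treatment value stands in for the missing one. Here no such value exists. For the week-6 endpoint the rule reduces to baseline carried forward, and it does so even for a patient who misses week 6 but returns at week 9 or 12.

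Two consequences follow. The arm means are pulled toward zero in proportion to the loss in each arm, so the contrasts depend on drop-out as well as on treatment. The imputed zeros also enter the ANCOVA as if observed, which makes the data look more numerous and less variable than they are.

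The rule affects follow-up as well. At weeks 9 and 12, when treatment has ended, it inserts the end-of-treatment value for patients lost after week 6 and the baseline value for those lost earlier. The durability estimate then reflects the rule as well as the patients.

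**Working it through.** **Inputs.** From the sample size paragraph: anticipated falls in 24-h SBP of 12 (affected meridian), 10 (non-affected), 3 (sham) and 0 mmHg (waiting list); SD 20; drop-out 15%; 107 enrolled per group. No diastolic values are given, so the working is for SBP.

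**Assumptions.** (a) All of the 15% is lost before week 6. (b) Patients who are lost would have had their arm's anticipated mean change. (c) Pooled verum means affected plus non-affected, mean (12 + 10)/2 = 11. If sham were also pooled against the waiting list, the mean would be (12 + 10 + 3)/3 = 8.33 and the same shrinkage would apply.

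**The plan's own figure.** The stated 93 per group was not reproduced from these inputs. At two-sided 5% and 90% power, affected versus sham (9 mmHg) needs 104–105 per group, and a four-group ANOVA needs 60. The 107 is 93 × 1.15 = 106.95. That is a separate matter; only the 107 is used below.

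**Formulas.** With a proportion d missing and imputed as zero, true mean change m:
- expected change = (1 − d) × m
- variance of change = (1 − d) × 20² + d × (1 − d) × m²

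**Equal loss of 15%.**

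| Contrast | True | Under the rule |
|---|---|---|
| Pooled verum − sham | 8.0 | 0.85 × 11 − 0.85 × 3 = 6.80 |
| Pooled verum − waiting list | 11.0 | 0.85 × 11 − 0 = 9.35 |
| Affected − sham | 9.0 | 0.85 × 12 − 0.85 × 3 = 7.65 |
| Affected − non-affected | 2.0 | 0.85 × 12 − 0.85 × 10 = 1.70 |

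For 5% to 25% missing, affected − sham runs from 8.55 to 6.75 mmHg.

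**Variance at 15%.**
- Affected: √(0.85 × 400 + 0.1275 × 144) = √358.36 = 18.9.
- Sham: √(340 + 0.1275 × 9) = √341.15 = 18.5.
- Standard error, affected − sham, under the rule: √((358.36 + 341.15)/107) = 2.56.
- Standard error from the 0.85 × 107 = 90.95 patients per arm actually observed: √(800/90.95) = 2.97.

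The reported standard error is thus about 14% too small for the information collected.

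**Power, affected versus sham, two-sided 5%, normal approximation.**
- Under the rule: Φ(7.65/2.557 − 1.96) = 84.9%.
- Completers: Φ(9/2.966 − 1.96) = 85.9%.

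The smaller difference and the smaller standard error nearly cancel. These figures are for a comparison of mean changes, not for the planned ANCOVA.

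**Unequal loss (illustrative rates, not in the protocol).**

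| Contrast (true) | Loss, first / second arm | Under the rule |
|---|---|---|
| Pooled verum − sham (8.0) | 25% / 10% | 0.75 × 11 − 0.90 × 3 = 5.55 |
| Pooled verum − sham (8.0) | 10% / 25% | 0.90 × 11 − 0.75 × 3 = 7.65 |
| Pooled verum − sham (8.0) | 5% / 25% | 0.95 × 11 − 0.75 × 3 = 8.20 |
| Affected − non-affected (2.0) | 10% / 25% | 0.90 × 12 − 0.75 × 10 = 3.30 |
| Affected − non-affected (2.0) | 25% / 10% | 0.75 × 12 − 0.90 × 10 = 0.00 |

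Pooled verum − sham is inflated only if 3 × (sham loss) exceeds 11 × (verum loss), that is, if sham loss is more than 3.7 times verum loss. Against a waiting list with mean 0, the contrast is (1 − d) × 11 and can only shrink.

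**The case against.** Several points on the other side stand.

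- **Not every drop-out is affected.** A reader might infer that each of the 15% is scored as zero. The protocol does not time that figure, and the study has six weeks of treatment and six of follow-up. Patients lost after week 6 keep an observed primary value, so the equal-loss figures are an upper case for a 15% rate.
- **Bias in the mean is conditional.** If patients who leave would truly have returned to baseline, zero is the right mean for them. In the waiting-list arm, where 0 mmHg is anticipated, zero is the right mean anyway. The bias rests on lost patients resembling their arm in the needled groups.
- **The efficacy contrasts mostly err on the cautious side.** It is tempting to say that the rule could readily manufacture efficacy. Under the plan's means it seldom would. With no true difference, an assumed shared fall of 5 mmHg and 10% against 25% loss, the false difference is 5 × 0.15 = 0.75 mmHg. That is about a third of its standard error of roughly 2.1–2.2, and its effect on the false-positive rate is small.
- **Durability need not be overstated.** Carrying week-6 values forward favours persistence if the effect wanes, while carrying baseline forward for early losses works against it. The net direction is unknown.
- **A per-protocol analysis is planned.** Agreement between the two sets gives some reassurance. It does not repair the intention-to-treat estimate, which still contains the imputed zeros.

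A separate analysis plan may add sensitivity analyses, and their absence here is not the point. The point is the rule that the article does state.

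**Conclusion.** The concern holds in this form. For every patient without a week-6 ambulatory reading, the stated rule fixes the primary change at zero. If lost patients resemble their arm, and the planned 15% falls before week 6 equally in all arms, every contrast shrinks by 15% and the SD of change falls from 20 to between 18.4 (√340, waiting list) and 18.9. Power is hardly touched, so the harm lies in the estimate and its stated precision rather than in the chance of a significant result.

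The contrast most exposed is affected versus non-affected meridians. It is one of the trial's stated aims, the anticipated difference is only 2 mmHg, and modest imbalance in loss can erase it or enlarge it by 1.3 mmHg. The week-9 and week-12 results are unreliable in a direction that cannot be known in advance. Because the effect on the main efficacy contrasts is moderate and mostly conservative, this is a point that should be fixed rather than one that invalidates the design.

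**What to change.** Drop last observation carried forward as the primary rule. Analyse the observed 24-h SBP at weeks 6, 9 and 12 with a likelihood-based repeated-measures model (arm, visit, arm-by-visit, baseline value, centre), taking the week-6 contrast as primary. Multiple imputation under missing-at-random is an acceptable alternative. Treat 24-h DBP in the same way. Add a delta-adjusted or control-based sensitivity analysis, keep baseline carried forward only as a labelled sensitivity analysis, and do not carry week-6 values into weeks 9 and 12.

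The cost is analysis wording and some programming, with no new patients or measurements. The downsides should be stated openly. The primary analysis would rest on missing-at-random, which the data cannot confirm. Patients with no ambulatory reading after baseline add little to the model, so for them it is close to a completer ANCOVA. The gain comes from patients who miss week 6 but are seen at week 9 or 12, from honest standard errors, and from the sensitivity analysis.

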Before randomization, all participants will undergo routine tests of blood, urine, stool sample, electrocardiogram examination, Doppler echocardiography, carotid ultrasonography, as well as blood biochemical tests (AST, ALT, BUN, Scr, fasting glucose, triglyceride, HDL cholesterol, LDL cholesterol, albumin/creatinine.). These tests will help identify and exclude participants with serious illnesses of the heart, liver, and kidneys, or other severe diseases.

Adverse events are defined as any unexpected or uncomfortable signs, symptoms, or diseases, regardless of the intervention. These adverse events include bleeding, hematoma, fainting, serious pain, and local infection. If any adverse events happen during the entire observation period, all the details should be documented in the case report form.

We have designed a case reported form containing a variety of information, and this will be completed by the corresponding researchers at each center. At each center, the obtained information will be recorded on an electronic database, for subsequent statistical analysis. During the observation period, if there are any drop-outs or withdrawals, the investigator must find out their reasons and record them in the case report form. The patients’ compliance during the 6 weeks of treatment and 6 weeks of follow-up will also be documented.

#### **
*Sample size calculation and statistical analysis*
**

According to the previous literature [26], the average 24-hSBP of hypertensive patients rose 1.6 mmHg after being treated by sham acupuncture, while the average 24-hSBP of hypertensive patients lowered 5.4 mmHg after being treated with verum acupuncture. Therefore, the adjusted mean difference between the two groups was 7 mmHg. In this study, we anticipated an 12 mmHg improvement by affected meridian acupuncture; 10 mmHg by non-affected meridian acupuncture; 3 mmHg by sham acupuncture; and 0 mmHg in the waiting-list group. The standard deviation is set as 20. We calculated this using 90% power at a 5% significance level with G*Power (version 3.1.2, Franz Faul, Universität Kiel, Germany), and the result showed an estimated 93 patients per group. Considering a drop-out rate of 15%, we plan to enroll 107 patients per group, 428 patients in total for the four different groups.

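### For SF-36, which has one post-treatment value, the named repeated-measures analysis amounts to an unadjusted change-score test; ANCOVA on the day-0 score would be more precise at no cost (minor)

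*Protocol article*

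**What the plan says.** All references are to the protocol article, the only document available.

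- **Primary outcome.** The section on sample size calculation and statistical analysis lists the arm comparisons for the primary outcome and closes the list with "The above analysis will be performed using the ANCOVA model".
- **Secondary outcomes.** The next paragraph of that section gives a different method: "The repeated measures analysis will be used in the different time point assessments for the secondary outcomes". It then assigns the Kruskal-Wallis test to skewed data. It does not state the role of the baseline value or which model term is tested.
- **SF-36.** The abstract lists it among the secondary endpoints. The section on secondary outcome measures words the outcome as "Changes in patients’ health-related quality of life, according to the SF-36" and fixes the schedule: "SF-36 investigates at 0 day and 6 weeks after randomization". Table 1 shows the same two visits.
- **Ambulatory pressures.** The blood pressure measurement section has four occasions: "The 24-h ambulatory blood pressure monitoring measures at baseline, 6 weeks, 9 weeks, and 12 weeks after randomization".

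**The concern.** A repeated-measures analysis needs at least two occasions per patient. SF-36 supplies one after treatment, so the only other occasion available is the pre-randomisation score. Used as an outcome level, that score contributes its full sampling noise to the treatment comparison. Used as a covariate, it removes noise.

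The Discussion expects acupuncture to improve health-related quality of life, and SF-36 is the instrument for that claim. A less precise test makes a real benefit easier to miss, although the more precise analysis needs only data already scheduled. What is at stake is precision on a secondary endpoint, not validity.

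**Working it through.** **Plan's own figure.** There is none to reproduce: the article gives no power, standard deviation or sample size for SF-36.

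**Inputs**
- Occasions: day 0 and week 6 (secondary outcome measures; Table 1).
- Significance level 5% and power 90%: "We calculated this using 90% power at a 5% significance level with G*Power". These belong to the primary outcome and serve here only as a reference point. Sidedness is not stated; two-sided is assumed.
- Correlation r between day-0 and week-6 scores: not in the document; assumed 0.3 to 0.7.
- Equal variance σ² at both occasions: assumed.

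**Step 1: what the group-by-time test is.** With two occasions, the interaction contrast between two arms is the difference in mean (week 6 − day 0), which is the change-score comparison. A numerical check on one simulated data set with 93 patients per arm gave an interaction F of 20.6057 and a squared t for the change score of 20.6057.

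**Step 2: bias.** In a simulation of 4,000 trials with 93 per arm, r = 0.5 and a true effect of 0.40 SD, the mean estimate was 0.400 for the change score (standard error 0.144) and 0.399 for ANCOVA (standard error 0.125). Both recover the true effect. Only the spread differs.

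**Step 3: variance per patient**
- Change score: σ² + σ² − 2rσ² = 2σ²(1 − r)
- ANCOVA: σ²(1 − r²)
- Ratio, ANCOVA to change score: (1 − r²) / [2(1 − r)] = (1 + r)/2

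The ratio does not depend on the number of patients or on which arms are contrasted.

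**Step 4: power.** For 90% power under ANCOVA at two-sided 5%, effect divided by standard error is 1.960 + 1.282 = 3.242. Under the change score this becomes 3.242 × √[(1 + r)/2], and power is Φ(that value − 1.960). The sample size ratio for equal precision is 2/(1 + r).

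| r | Variance ratio (1 + r)/2 | Effect / SE, change score | Power, change score | Patients needed relative to ANCOVA |
|---|---|---|---|---|
| 0.3 | 0.65 | 3.242 × 0.806 = 2.613 | Φ(0.653) = 74% | 1.54 |
| 0.5 | 0.75 | 3.242 × 0.866 = 2.807 | Φ(0.847) = 80% | 1.33 |
| 0.7 | 0.85 | 3.242 × 0.922 = 2.989 | Φ(1.029) = 85% | 1.18 |

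The loss shrinks as r rises; at r = 0.8 the change score has 87% power.

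**The case against.** **The sentence may not cover SF-36.** It is limited to assessments at different time points, and it cannot literally cover every secondary measure, because the treatment-response questions are asked once: "Response to the treatment will be measured at the end of treatment, using a five-point Likert self-administered scale". It could be meant only for the ambulatory pressures. This is possible, but SF-36 is a secondary outcome assessed at two time points and defined as a change, so the natural reading includes it. If it is excluded, the only other method the article offers is Kruskal-Wallis for skewed data, which is not baseline-adjusted either.

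**The role of baseline may be settled elsewhere.** The article is condensed and the full statistical plan is not shown. A repeated-measures model with day 0 as a response and a common baseline mean across arms would give essentially the ANCOVA estimate, and the text does not exclude it. This stands, and it is a reason to rate the point low. The article also names no covariate for the primary ANCOVA, so a claim that primary and secondary results will not be comparable is not supported.

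**A change score is a legitimate analysis.** Agreed: it is unbiased under randomisation, and its cost is precision only.

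**Stronger readings that a reader might infer.**
- *The treatment effect is halved.* This would follow if the group main effect over day 0 and week 6 were taken as the treatment test, because it averages a zero difference at baseline with the week-6 difference. The article nowhere says that this term will be tested.
- *The ambulatory outcomes share the fault.* They have three post-baseline visits, so nothing forces baseline into the outcome vector. A model of weeks 6, 9 and 12 with baseline as covariate is itself a repeated-measures analysis and fits the stated wording. Nor does the article say that it will average over visits.

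**Conclusion.** The point holds for SF-36 only, as a free improvement of minor severity. On the natural reading, an ordinary repeated-measures analysis of two occasions gives the unadjusted change-score comparison as its group-by-time test. Against baseline-adjusted ANCOVA this costs 18–54% more patients for equal precision, or a fall from 90% to about 74–85% power. These figures rest on an assumed correlation of 0.3–0.7, equal variances at the two occasions and a two-sided 5% test; the 90% is a reference level, not a power that the article claims for SF-36. No bias is shown, and no error is shown in the method for daytime and night-time pressure or pulse pressure.

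**What to change.** State that the week-6 SF-36 scores will be analysed by ANCOVA with the day-0 score as covariate (or by a repeated-measures model with the baseline mean constrained equal across arms), using the same arm contrasts as the primary outcome. Add that no group main effect averaging in the day-0 value will be used as the treatment test. The ambulatory outcomes need no correction on this point; a sentence confirming a model of weeks 6, 9 and 12 with baseline as covariate would be a clarification only.

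The cost is one or two sentences and a few lines of code. No extra patients, visits or data are needed, because Table 1 already schedules the day-0 SF-36.

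### The Kruskal-Wallis test named for skewed data cannot use baseline or centre, and as a single four-arm test it cannot separate verum from sham; a baseline-adjusted rank test of the planned contrasts would be better (minor)

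*Protocol article*

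**What the plan says.** All of this is in the Protocol article, section Sample size calculation and statistical analysis.

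The primary outcome has three comparisons:
- "For the primary outcome, we will run a comparison between pooled acupuncture groups and waiting list control group"
- "We will then run another comparison between the pooled acupuncture groups and sham acupuncture group"
- "Finally, a comparison between acupuncture groups will be run to see if selecting points along meridians was a better treatment option"

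Their method and multiplicity rule follow: "The above analysis will be performed using the ANCOVA model" and "Multiple comparisons will be adjusted according to the Bonferroni correction method".

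A new paragraph then opens with the secondary outcomes: "The repeated measures analysis will be used in the different time point assessments for the secondary outcomes". The next sentence is the one at issue: "The Kruskal-Wallis test will be employed in the analysis of skewed distribution data". It names no outcome, number of groups, trigger for calling data skewed, or follow-up comparison.

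Elsewhere the article says that randomization is stratified by centre (Randomization). Ambulatory pressure and SF-36 are recorded at day 0 and again at 6 weeks, and the two five-point response items only at the end of treatment (Table 1, Outcome measurement).

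**The concern.** The trial asks three separate questions: acupuncture against no treatment, verum against sham, and affected against non-affected meridians. Kruskal-Wallis is the k-sample rank test. Over four arms it asks only whether the arms differ somewhere, and it gives no effect estimate for any of the three questions.

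The waiting list is untreated and its patients know it, and several secondary outcomes are self-reported. A gap between needled and waiting patients with no gap between verum and sham is therefore a realistic result, and a lone omnibus p-value could not tell it from a verum effect.

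The test also has no place for a baseline value or a centre term, although the trial collects the first and stratifies on the second. For outcomes with a day-0 value, that gives up precision already paid for.

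**Working it through.** The plan gives no power figure for a rank test, so there is none to reproduce. Inputs from the sample size section: 93 evaluable per group (taken as given), expected improvements of 12, 10, 3 and 0 mmHg, SD 20, and a 5% level. Assumed here: two-sided testing, baseline correlations, and a log-normal shape for skewed data. Pooled acupuncture means AMA plus NMA. Centre effects are not modelled, and all power figures are at 5% without Bonferroni.

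**1. Four-arm test when verum equals sham.** Kruskal-Wallis is approximated by a noncentral chi-square with 3 degrees of freedom and λ = 0.955 × N × V / SD². Here N = 4 × 93 = 372, V is the variance of the four means (divisor 4), and 0.955 is the efficiency of ranks for normal data. If all needled arms improve by m and the waiting list by 0, V = 3m²/16.

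| m (mmHg) | m/SD | V | λ | rejects |
|---|---|---|---|---|
| 3 | 0.15 | 1.69 | 1.50 | 15% |
| 6 | 0.30 | 6.75 | 6.00 | 52% |
| 10 | 0.50 | 18.75 | 16.65 | 94% |
| 12 | 0.60 | 27.00 | 23.98 | 99% |

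Simulation gave 15%, 52%, 95% and 99%. In the same runs the verum-sham contrast rejected in 4.8% to 5.7%, as it should.

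**2. Four-arm test at the planned means.** For 12, 10, 3 and 0, V = 24.19 and λ = 0.955 × 372 × 24.19 / 400 = 21.48, which gives 98% power. The unadjusted contrast of pooled verum with sham is (12 + 10)/2 − 3 = 8 mmHg. Its SE is 20 × √(1.5/93) = 2.54, so power is Φ(8/2.54 − 1.96) = Φ(1.19) = 88%. The omnibus test is the more powerful of the two, but for a different question.

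**3. The same contrast with and without baseline.** Take a shift of 0.35 SD on the log scale for pooled verum against sham.
- Unadjusted rank test: 0.35/√(1.5/93) = 2.756. Multiplied by √0.955 this is 2.693, and Φ(2.693 − 1.960) = 77%.
- Rank ANCOVA: divide 2.693 by √(1 − r²), where r = (6/π) arcsin(ρ/2) is the rank correlation.

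| ρ | r | statistic | power |
|---|---|---|---|
| 0.3 | 0.288 | 2.81 | 80% |
| 0.5 | 0.483 | 3.07 | 87% |
| 0.7 | 0.683 | 3.69 | 96% |

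Simulation with log-normal data (sigma 0.6) gave 76–77% unadjusted and 79–80%, 86% and 96% adjusted, with type I error near 5% throughout.

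**4. Ranking change scores instead.** In the same simulation, a rank test of change from baseline had 61%, 76% and 93% power at ρ = 0.3, 0.5 and 0.7. Each is below rank ANCOVA.

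**5. Raw-scale ANCOVA as the alternative.** If the treatment adds a constant on the raw scale of skewed data (0.35 SD, ρ = 0.5), ANCOVA with robust standard errors has 85–86% power, the plain rank test 96%, and rank ANCOVA 98–99%. The better replacement is therefore a rank method that uses baseline.

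**The case against.** Several points on the other side are right, and they limit the concern.

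- **Reach.** A reader might infer that skewness would switch the primary analysis away from ANCOVA. The text does not say so. The sentence follows the one on secondary outcomes, and the three contrasts are tied to the primary outcome and to ANCOVA. The wording is unrestricted, so an explicit exemption is worthwhile, but no contradiction is shown.
- **Omnibus only.** A reader might infer one four-arm test and nothing after it. With two groups Kruskal-Wallis is the rank-sum test, and the Bonferroni sentence leaves room for pairwise follow-up. The omnibus criticism is conditional on that reading.
- **False positives.** A rejection caused by the waiting list is not a type I error, since the four arms do differ. The risk lies in interpretation, and at the article's own sham-against-waiting-list gap (3 mmHg, 0.15 SD) the rate is only 15%.
- **Power.** A general loss of power is not supported, as steps 2 and 5 show.
- **Baseline and centre.** The article lists no covariates for its models, so no stated centre adjustment is being withdrawn. The response items have no baseline to lose.
- **Condensation.** Triggers, covariates and follow-up tests may be left to the full analysis plan, and their absence here is no fault.

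What survives is that the article names a particular test. That test cannot take the baseline or the centre under any reading. A later plan with adjusted contrasts would have to depart from the published statement.

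**Conclusion.** The point holds in a limited form and is minor. For skewed secondary outcomes with a day-0 value, the named test is weaker than a baseline-adjusted rank test of the same contrast: about 77% against 80% to 96% power. This rests on 93 per arm, a 0.35 SD log-scale shift and assumed correlations of 0.3 to 0.7. At the lowest correlation the gain is only about 3 percentage points. If the test is run once over four arms, its result cannot be read as evidence for verum over sham. Nothing here shows invalid error rates or a fault in the primary analysis.

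**What to change.** Replace the sentence with three statements.

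1. It does not apply to the primary outcome, which stays with ANCOVA.
2. Skewed continuous secondary outcomes are analysed by rank ANCOVA adjusted for baseline and centre. It tests the same three contrasts: pooled acupuncture against waiting list, pooled acupuncture against sham, and AMA against NMA. The method for each outcome is fixed before the statisticians learn the allocation, not chosen from outcome data by arm.
3. The two five-point response items are reported by the same contrasts with a centre-stratified rank test or an ordinal model, not by an omnibus test alone.

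The cost is wording and minor programming, with no new data. The drawback is that a rank-based test gives a less direct effect estimate, so a descriptive difference on the original scale should be shown beside it.
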